## Background

Westernization of lifestyle has led to an explosive increase in the number of diabetic patients and an increase in diabetic atherosclerosis in Eastern Asian countries [1,2]. This is of great concern for the future of patients and health systems in East Asia, and is a problem that requires immediate and careful evaluation. With this in mind a cooperative, multinational research group in Japan, Korea, China, and Phillippine has been formed to investigate the potential for antiplatelet medication to prevent the occurrence and progression of diabetic atherosclerosis in Asian patients.

The rationale for the study is based upon the finding that the primary incidence rate of coronary artery disease (CAD) in diabetic patients is similar to the secondary incidence rate of CAD in nondiabetic patients. This finding suggests that secondary treatment of atherosclerosis is applicable to the primary prevention of arteriosclerosis in diabetic patients. Antiplatelet drugs are widely reported to be effective in preventing the recurrence of atherosclerosis. In one study [3], type 2 diabetic patients with early-stage carotid atherosclerosis who were given aspirin showed a slight progression of intima-media thickness (IMT) of the carotid artery (0.033 ± 0.010 mm/year). In another study [4], similar patients given cilostazol showed negligible change in IMT (0.00 ± 0.16 mm/3 years). However, the primary preventive and secondary therapeutic effects of these two drugs have not been sufficiently investigated in the Asian diabetic patient population. We therefore initiated an international, 2-year prospective follow-up interventional study to clarify the efficacy and usefulness of aspirin and cilostazol in the primary prevention and secondary treatment of diabetic atherosclerosis in Asian patients. Assessment will be performed by chronologically observing the intima-media thickness (IMT) of the carotid artery, which is used as a surrogate endpoint of atherosclerosis, and by analyzing the occurrence and progression of large-vessel complications in patients with type 2 diabetes and mild atherosclerosis [5,6].

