**Secondary endpoints:**	
IMT*: Variation of right and left max IMT-ICA	

*Variation is measured by the IMT Evaluation Committee by using a diagnostic software application called IntimaScope^® ^while the allocations are blinded.

The following exclusion criteria were set: those with type 1 or secondary diabetes, severe ASO (greater than a Fontaine IIb category) or grade 4 or higher cerebral infarction on the Modified Rankin Scale, and medical history of angina or myocardial infarction. In addition, patients with a range of concomitant comorbidities including severe hepatic or renal dysfunction, congestive heart failure, bleeding disorders, or familial hypercholesterolemia, those with allergy or hypersensitivity to the investigational drugs, pregnant or lactating women, or women wishing to become pregnant, were excluded. Written informed consent has been obtained from all patients, and the study has been reviewed by the ethics review board of the all institutes participated in this study if the institute had the ethics review board.

Registration of patients was preformed at the administration office of the Diabetic Atherosclerosis Prevention by Cilostazol (DAPC) Study via the Internet, and once enrolled, subjects were randomly assigned to the aspirin group (81–100 mg/day; group A) or the cilostazol group (100–200 mg/day; group C). Patients who were already receiving antiplatelet drugs were assigned without a washout period. The study period will be 2 years after the registration of subjects (registration period: November 2004 to March 2006; full study duration: December 2004 to March 2008).

The primary study endpoint is the change in right and left maximum IMT of the common carotid artery (CCA) and mean IMT-CCA change. Secondary endpoints are the change in right and left maximum IMT of the internal carotid artery; semiquantitative evaluation of cerebral infarction by MRI measurement; cardiovascular events including sudden death, occurrence or recurrence of stroke, transient cerebral ischemic attacks, acute myocardial infarction, angina, and progression of ASO; overall death; withdrawal; and change in ABI.

Investigations will be performed at the start of the study, after 1 year, at the conclusion of the study, and at the time of any discontinuations or changes in dosage. Any adverse reactions will also be assessed.

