Statistical analysis using changes in IMT was first undertaken to determine the number of patients required to identify a significant difference between the two groups. As a result, at least 408 patients were calculated to be required to obtain a significant difference (*p *< 0.05) between the two groups. Therefore, the target number of patients was 400 for the 1-year registration period. Statistical analysis will be performed using the *t*-test to compare the change in maximum IMT, the log-rank test for incidence of events and mortality rate, and the Kaplan-Meier method to plot survival curves. Ratios of events between the 2 groups and confidence intervals are to be determined by Cox regression. A 1-way ANOVA will be used to compare ABI. The administrative office of the DAPC Study will analyze these data.

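### The primary t-test on IMT change is valid but fixes the baseline coefficient at 1; ANCOVA with baseline IMT as covariate would be more precise for one degree of freedom

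*Protocol article*

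**What the plan says.** In the Protocol article, under Study design and protocol, the primary endpoint is defined as follows: "The primary study endpoint is the change in right and left maximum IMT of the common carotid artery (CCA) and mean IMT-CCA change". On timing it says: "Investigations will be performed at the start of the study, after 1 year, at the conclusion of the study". An IMT change cannot be formed without the starting value, so every patient who contributes to the primary analysis has a baseline IMT.

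The statistical analysis paragraph of the same section assigns the t-test "to compare the change in maximum IMT, the log-rank test for incidence of events and mortality rate". It names no covariate, and baseline adjustment appears nowhere else in the article. The footnote to Table 2 says that IMT variation is measured by an IMT Evaluation Committee with one software package, with allocation blinded.

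**The concern.** Maximum IMT is measured with error, and a maximum is a noisy summary. Patients whose baseline reading is high by chance tend to show a smaller later increase, so change is negatively related to baseline. Randomisation balances baseline IMT on average but not exactly in any one trial. If one arm happens to start thicker, regression to the mean will make that arm appear to progress less, and an unadjusted comparison of changes does not remove this.

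The same relation between baseline and change is variance that a covariate could explain. Left unexplained, it widens the confidence interval of the primary comparison. At stake are some power and some protection against a chance imbalance, both available from data the trial already collects.

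**Working it through.** **Inputs from the article.** Total number: "at least 408 patients were calculated to be required to obtain a significant difference". The significance level is 0.05. I assume 204 per arm and a two-sided test; neither is stated.

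**Input not in the article.** The baseline to 2-year correlation rho, taken over 0.5 to 0.95. Equal variance σ² at both visits is also assumed.

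**The plan's own figure.** The 408 cannot be reproduced, because power, target difference, SD of change and dropout are not given. The Background reports "0.033 ± 0.010 mm/year" on aspirin and "0.00 ± 0.16 mm/3 years" on cilostazol, but does not say that these were sample-size inputs. A 2-year difference of 2 × 0.033 = 0.066 mm with SD 0.16 mm would need 186 patients for 80% power or 248 for 90%. Several arbitrary combinations land near 408, so a match would identify nothing. The comparison below needs only the ratio of variances, so it does not depend on how 408 arose.

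**Step 1: variance of the change score.** Var(change) = 2σ²(1 − rho).

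**Step 2: variance after adjustment.** The slope of change on baseline is −(1 − rho). The residual variance is 2σ²(1 − rho) − (1 − rho)²σ² = σ²(1 − rho²).

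**Step 3: ratio.** σ²(1 − rho²) / [2σ²(1 − rho)] = (1 + rho)/2.

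**Step 4: effect of a chance imbalance.** A baseline difference d between arms shifts the difference in change by −(1 − rho)d. If d equals one standard error of the baseline difference, σ√(2/204), the shift is √((1 − rho)/2) standard errors of the change comparison.

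| Assumed rho | Variance ratio | ANCOVA N equal to 408 by t-test | Power if t-test has 80% | Power if t-test has 90% | Share of imbalance carried over | Shift from 1-SE imbalance (in SEs) |
|---|---|---|---|---|---|---|
| 0.5 | 0.75 | 306 | 90% | 96% | 0.50 | 0.50 |
| 0.7 | 0.85 | 348 | 86% | 94% | 0.30 | 0.39 |
| 0.8 | 0.90 | 368 | 84% | 93% | 0.20 | 0.32 |
| 0.9 | 0.95 | 388 | 82% | 91% | 0.10 | 0.22 |
| 0.95 | 0.975 | 398 | 81% | 91% | 0.05 | 0.16 |

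**Step 5: cost.** Estimating one more coefficient inflates variance by about 1/404, or 0.25%. ANCOVA stays ahead while (1 + rho)/2 × (1 + 1/404) < 1, that is, for rho below about 0.995.

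**Step 6: simulation.** In 4,000 simulated trials with 204 per arm, type I error was about 5% for both methods. Power for t-test against ANCOVA was 0.80 against 0.89 (rho 0.5), 0.79 against 0.86 (rho 0.7) and 0.80 against 0.82 (rho 0.9).

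**Can rho be narrowed?** Only with a further assumption. If ±0.16 mm is a patient-level SD of change and applies here, rho = 1 − 0.16²/(2σ²). Assumed cross-sectional SDs of 0.20, 0.30 and 0.40 mm then give 0.68, 0.86 and 0.92. The article gives no cross-sectional SD, so the full range stays.

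**The case against.** The strongest defence is that the planned test is conventional and sound. Under randomisation it is unbiased and holds its 5% level, so nothing in the article is wrong in the sense of an invalid inference. That stands. The article is also condensed, and covariates are often left to a fuller plan. This carries less weight, because the article does not stay silent: it names an unadjusted test for the primary endpoint.

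Some stronger readings are tempting but not supported:

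- A reader might infer that the t-test throws baseline IMT away. It does not: change is follow-up minus baseline, so baseline enters with a fixed coefficient.
- A reader might infer that a baseline imbalance passes in full into the result. Only the share (1 − rho) does, which is 10% at rho 0.9.
- A reader might infer that ANCOVA makes good the gap between the 408 required and the target of 400. That holds only if (1 + rho)/2 < 400/408, so rho below about 0.96, and the gap is a separate matter.
- A reader might infer that country must also be adjusted for. Reading is blinded and by one committee, and within-patient change cancels any constant country or scanner offset. Image acquisition and patient mix may still differ, but no figure in the article shows that IMT change differs by country.

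**Conclusion.** The point holds as one of efficiency and of protection against chance imbalance. It does not show an invalid primary analysis or a wrong sample size. Baseline-adjusted ANCOVA would reduce the variance of the primary comparison by about 25% at rho 0.5, 10% at rho 0.8 and 2.5% at rho 0.95, before the 0.25% cost of one degree of freedom. If IMT is highly reproducible over 2 years, the gain is small.

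The direction is secure for any rho below about 0.995, given equal variances at the two visits. The size is not secure, because it rests on a correlation that the article does not report.

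**What to change.** Before unblinding, replace the t-test as the primary analysis with an ANCOVA of 2-year change in maximum IMT-CCA on treatment group, with the corresponding baseline IMT as covariate. The article defines the endpoint by right and left maximum and gives no single patient-level maximum, so each change should be paired with the baseline of the same measure. Report the adjusted difference with its 95% confidence interval, and keep the t-test as a supportive analysis. Use the same model for mean IMT-CCA and for maximum IMT-ICA. A country term is optional; its gain has not been quantified.

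The cost is a short change to the analysis paragraph and one degree of freedom per model. It needs no new measurement and adds no burden for patients.

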**Results:**

The primary study endpoint was changes in right and left maximum intima-media thickness of the common carotid artery. Secondary endpoints include changes in right and left maximum intima-media thickness of the internal carotid artery; semiquantitative evaluation of cerebral infarction by magnetic resonance imaging; cardiovascular events including sudden death, stroke, transient cerebral ischemic attacks, acute myocardial infarction, angina, and progression of arteriosclerosis obliterans; overall death; withdrawal; and change in ankle-brachial pressure index.

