***Inclusion criteria:***
1) Type 2 diabetes mellitus
2) Age between 40 to 85 years
3) Clinical findings suggestive of arteriosclerosis obliterans (ASO)
Note 1: Definition of ASO: Patient who has the following lesions in either of the lower limbs
• ABI (ankle brachial pressure index) < 1.0
• A weakened or bilaterally different pulsation of popliteal artery or dorsal artery of foot
• clinical signs and symptoms suggestive of ASO

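### The endpoint is change in ABI, but the stated 1-way ANOVA names only ABI and has no baseline term; adjusting for baseline ABI would be a free gain in precision

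*Protocol article*

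**What the plan says.** The endpoint is defined twice, and consistently. The abstract (Results) lists "change in ankle-brachial pressure index" among the secondary endpoints. The endpoint paragraph of Study design and protocol ends its list with "overall death; withdrawal; and change in ABI".

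The statistical paragraph just before the Discussion gives the analysis in one sentence: "A 1-way ANOVA will be used to compare ABI". It names no change score, time point or baseline covariate. A few lines earlier in that paragraph, the t-test is planned "to compare the change in maximum IMT", so change is spelled out for one continuous endpoint and not for the other.

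Baseline ABI should be available. Table 1 lists "ABI (ankle brachial pressure index) < 1.0" among the findings that define arteriosclerosis obliterans at entry, and the visit schedule reads "Investigations will be performed at the start of the study, after 1 year, at the conclusion of the study".

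**The concern.** The analysed variable, as written, is not the endpoint variable. Read literally, the sentence compares ABI values between the arms and ignores where each patient started. If ABI is stable within patients, much of the spread at follow-up is spread that was already there at entry. An analysis without a baseline term leaves that spread in the error variance.

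The sentence can also be read as shorthand for a comparison of changes. That matches the endpoint, but it still does not use the baseline as efficiently as it could be used. Because the text fits both readings, it leaves open which variable, and which visit, will be reported. At stake are the width of the confidence interval for one secondary endpoint and a clear link between that endpoint and its test.

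**Working it through.** **The plan's own figure.** There is none for ABI. The only sample-size statement is that "at least 408 patients were calculated to be required to obtain a significant difference", and it rests on changes in IMT. Its difference, SD and power are not stated, so 408 cannot be confirmed. Several guessed IMT inputs reach it; for example, a difference of 0.033 mm, SD 0.16/√3 mm, 95% power, two-sided, gives exactly 408. Below, 408 serves only as a scale.

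**Inputs.**
- Two randomised arms (Table 2; Study design and protocol). Equal allocation is assumed because no ratio is given.
- Correlation rho between baseline and 2-year ABI: not in the document. Assumed 0.5, 0.7 and 0.8, with 0.3 as a low case.
- ABI variance σ², assumed equal at baseline and follow-up.

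**Step 1: is the named test wrong in kind?** With two groups, a 1-way ANOVA and the t-test are the same test. In one simulated data set of change scores, F = t² = 9.538 and p = 0.00215 for both. An ANOVA on change scores would be a valid test of the stated endpoint.

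**Step 2: do follow-up ABI and change in ABI estimate different effects?** No. Baseline means are equal in expectation after randomisation, so subtracting baseline leaves the expected difference unchanged. In 5,000 simulated trials (408 patients, rho 0.7, SD 0.15, true difference 0.03, all assumed), the mean difference was 0.0297 for follow-up values and 0.0300 for changes. The standard errors were 0.0148 and 0.0115.

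**Step 3: what does baseline adjustment gain?** Per-patient variance entering the comparison:
- follow-up value only: σ²
- change score: 2(1 − rho)σ²
- ANCOVA with baseline: (1 − rho²)σ²

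Hence ANCOVA relative to follow-up only is 1 − rho². ANCOVA relative to the change score is (1 − rho²)/[2(1 − rho)] = (1 + rho)/2.

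| rho (assumed) | Change score ÷ follow-up only | ANCOVA ÷ follow-up only | ANCOVA ÷ change score |
|---|---|---|---|
| 0.3 | 1.40 | 0.91 | 0.65 |
| 0.5 | 1.00 | 0.75 | 0.75 |
| 0.7 | 0.60 | 0.51 | 0.85 |
| 0.8 | 0.40 | 0.36 | 0.90 |

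In patients, at rho 0.5, 0.7 and 0.8:
- The precision of 408 analysed on follow-up ABI alone is reached by ANCOVA with 306, 209 and 147 (408 × 0.75, 0.51, 0.36, rounded up).
- The precision of 408 analysed on change scores is reached with 306, 347 and 368 (408 × 0.75, 0.85, 0.90, rounded up).

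**Step 4: does the direction depend on rho?** Against follow-up only, ANCOVA is better for any non-zero rho; against the change score, for any rho below 1. The change score beats follow-up only just when rho exceeds 0.5. Inserting the word change into the sentence would therefore restore consistency but would not by itself guarantee a gain in precision.

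**The case against.** The strongest reply is that the sentence comes from a condensed article and ABI may simply be short for the endpoint defined a few paragraphs earlier. An unadjusted comparison in a randomised trial is valid, and covariates are commonly left to a full protocol or analysis plan. Much of this stands. The literal reading is the more likely one, given the contrast with IMT, but it is not certain. Nothing here shows an invalid test. What remains is that the article does fix a method and a variable: the variable does not match its own endpoint, and the method can be bettered at no cost whichever reading is meant.

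Several stronger inferences are tempting and are not supported:
- *The ANOVA tests a different quantity or misses the endpoint.* Step 2 shows that the expected treatment difference is the same.
- *Baseline differences in peripheral disease bias the comparison.* After randomisation only chance differences remain, and the standard error covers them.
- *Regression to the mean after selection on low ABI distorts the result.* Any such drift affects both randomised arms alike, and ABI is not the only finding in the entry definition.
- *The two legs will be counted as independent observations.* The document does not say so, and how limbs are handled is a detail that an article may leave to the full protocol.
- *The analysis needs about twice as many patients.* The factor 1/0.51 = 1.96 holds only at rho 0.7 and only under the literal reading.

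**Conclusion.** The point holds as a free improvement. The endpoint is change in ABI; the analysis sentence says ABI and has no baseline term. The cost is lost precision and a loose link between endpoint and test, not bias.

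For assumed rho between 0.5 and 0.8, baseline adjustment would cut the variance by 25% to 64% if follow-up values are what is compared, and by 25% to 10% if change scores are. These sizes rest on the assumed rho and on equal variances at the two visits. The direction of the gain does not rest on the value of rho. The endpoint is secondary, and neither the primary IMT comparison nor the target of 408 is affected.

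**What to change.** Replace the ABI sentence in the statistical paragraph with: *Change in ABI at 2 years is compared between groups by ANCOVA with baseline ABI as covariate, one value per patient.*

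This names the endpoint variable, the time point and the unit of analysis. With baseline in the model, the estimated treatment difference is the same whether the outcome is entered as the 2-year value or as the change, so the ambiguity disappears. The rule that yields one value per patient can be set in the analysis plan before unblinding.

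The cost is one sentence. No measurement is added, because an endpoint defined as change already requires a baseline ABI. If a full analysis plan already specifies this model, only the article's sentence needs to be aligned with it.

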## Discussion

The aim of this study is to clarify the efficacy and usefulness of two different antiplatelet drugs, aspirin and cilostazol, in the prevention of occurrence or progression of atherosclerosis in patients with type 2 diabetes. Antiplatelet drugs such as aspirin have been shown to be effective in preventing the recurrence of atherosclerosis in these patients. However, effectiveness of aspirin on diabetic patients is still controversial. Kodama and colleagues [3] have reported that both aspirin and ticlopidine significantly reduced, but did not halt, progression of increase in IMT in patients with type 2 diabetes and early-stage carotid atherosclerosis. Recently, the Primary Prevention Project (PPP) Trial showed that a significant reduction of the total cardiovascular events was observed in nondiabetic subjects but no significant reduction was observed in diabetic subjects [7]. In contrast, Shinoda-Tagawa and colleagues [4] showed that similar patients given cilostazol showed a negligible change in IMT over a 3-year follow-up period. Cilostazol is also shown to be effective in reducing occurrence of cerebral infarction in diabetic subjects [4]. We feel that the therapeutic effects resulting from the differing mechanisms of action of aspirin and cilostazol have not been sufficiently investigated in this patient population.

The results of this study are expected to assist in the development of appropriate drug therapies for patients with type 2 diabetes and atherosclerosis. This is a very important objective because the incidence of this common complication of diabetes is rising at a staggering rate among many Asian countries. It is expected that health systems in Asia will be severely stretched in the near future by trying to manage patients with diabetic complications, and the economic and social costs to the individuals and countries will be large. The design of this study is ground breaking in that enrollment was via the Internet and all results will be pooled by using a unique online patient registry system. Not only are all of the mathematical and demographic data to be held on this database, but also all of the images taken from the MRI assessment of cerebral changes and alterations in IMT. This is the first such online system to be developed in Asian countries for pooling data from an international clinical trial. Results will be available rapidly, and these findings are expected to provide clinical data that will help in the prevention of diabetic atherosclerosis and subsequent cardiovascular and cerebrovascular disease. Results from this important clinical trial are planned to be published in 2008.
